### Interventions

2.4

The present intervention involves a 3‐month program led by a Master's degree nursing student under the supervision of a nursing faculty member specializing in ethics education. Both groups will receive traditional training based on the professional ethics and relationships course included in the nursing curriculum, typically taken in the second semester. This course covers topics such as ethical principles, communication skills, and professional behavior.

The intervention group, in addition to traditional training, will participate in a specialized, scenario‐based workshop designed to deepen their understanding of moral concepts, strengthen their moral courage, and develop the skills and confidence needed to address complex ethical challenges. This approach immerses students in realistic clinical scenarios, enabling them to better grasp ethical principles and apply them effectively in practice.

The intervention consists of two workshop sessions, online education, and follow‐ups over 3 months. After obtaining written consent, both groups will complete a demographic questionnaire. Figure 1 illustrates a schematic representation of the study design.

**Figure 1 hsr271021-fig-0001:**
[figure not shown]
Schematic representation of the study design.

#### Scenario‐Based Moral Concepts Workshop for the Intervention Group

2.4.1

A moral concepts workshop will be held for the intervention group. At the beginning of the first workshop, after obtaining students' phone numbers, a collaborative group will be created on an internet‐based social media platform (WhatsApp). This group will include the researcher and the nursing ethics professor from the School of Nursing, Tehran University of Medical Sciences, to enhance the training, provide long‐term follow‐ups, and monitor the students in various aspects. The intervention group will receive the educational program on moral concepts through two 2‐h workshops over 2 consecutive days. In the first workshop, the basic principles of medical ethics will be discussed, and in the second, concepts derived from these principles will be analyzed.

The pedagogical approach used in this training intervention was based on constructivist and experiential learning models. This approach emphasizes active participation, collaborative problem‐solving, and reflective thinking. Through scenario‐based learning, students are exposed to complex ethical dilemmas similar to those encountered in real clinical settings, allowing them to apply theoretical knowledge in a practical, decision‐oriented environment. The intervention was designed to encourage critical thinking, moral reasoning, and confidence in ethical decision‐making.

The curriculum of the training was structured around the four core principles of biomedical ethics—autonomy, beneficence, nonmaleficence, and justice—as well as key derived ethical concepts such as confidentiality, honesty, disclosure, and moral courage. These concepts were selected based on the foundational biomedical ethics framework proposed by Beauchamp and Childress, and the professional codes of ethics developed by the American Nurses Association (ANA) and the International Council of Nurses (ICN). Their contextual relevance and educational priority were confirmed through expert review by ten faculty members specializing in nursing ethics at Tehran University of Medical Sciences.

All educational materials, including the ethical scenarios, were developed by the research team and underwent face and content validity review by ten faculty members with expertise in nursing ethics at Tehran University of Medical Sciences. This review process ensured that the scenarios reflected realistic, ethically significant clinical challenges. The training methodology integrated small group discussions, interactive scenario analysis, and weekly follow‐up activities, all designed to foster ethical sensitivity and professional growth among participants.

The workshops were cofacilitated by a nursing faculty member specializing in ethics education and a trained research assistant in nursing, ensuring both academic rigor and interactive student engagement. The faculty member led the educational discussions and scenario analyses, while the assistant coordinated the sessions and provided ongoing support throughout the training period.

During the workshop sessions, as well as while reviewing and analyzing the scenarios, both the researcher and a faculty member specializing in ethics will be present to answer any questions that may arise. In the intervention, the researcher and the faculty member, an expert in teaching ethics, will actively participate in all in‐person sessions, ensuring comprehensive guidance and support for the participants. Table 1 refers to the details of the ethics workshop.

**Table 1 hsr271021-tbl-0001:** Workshop topics details table in two sessions.

Activity headings	Details covered	Time schedule
*First Workshop: Training on Core Principles of Medical Ethics (2 h)*		
Introduction to Ethical Principles	The workshop began with an introduction to the core principles of medical ethics, including Beneficence, Nonmaleficence, Justice, and Autonomy. The instructor explained each principle, its importance in professional decision‐making, and used clinical examples for better understanding.	20 min
Group Case Analysis	Students were divided into small groups, with each group receiving a clinical case related to an ethical principle. Groups identified ethical dilemmas and proposed solutions aligned with the discussed principles. The results of their analyses were then presented to the larger group.	30 min
Group Discussion and Feedback	All groups shared their results, followed by a general discussion on different decisions. The instructor facilitated the session by highlighting key points and exploring various solutions.	20 min
Analysis of Complex Cases	Groups analyzed more complex scenarios involving multiple ethical dilemmas. They had to select the best solutions while considering various conditions and explain how ethical principles influenced their decisions.	40 min
Summary and Feedback	The instructor provided feedback on the analyses and emphasized critical points students should consider in real‐life situations.	10 min
*Second Workshop: Training on Concepts Derived From Ethical Principles (2 h)*		
Introduction to Derived Ethical Concepts	This session introduced ethical concepts such as Confidentiality, Honesty, Disclosure, and Moral Courage. The instructor explained their connection to core ethical principles and their application in clinical decision‐making.	20 min
Advanced Case Analysis	Groups received cases involving multiple conflicts between ethical principles and concepts. They analyzed these cases and proposed solutions that balanced various ethical values.	40 min
Group Review and Critique	Each group presented their analysis to the class, and other students critiqued their work. This session enhanced critical evaluation and analytical thinking skills.	30 min
Experience Sharing and Open Discussion	Students shared their experiences and perspectives on similar cases encountered in clinical settings. These discussions deepened understanding and practical application of taught concepts.	20 min
Final Summary and Feedback	The instructor provided final feedback on students' performances and highlighted key areas for improving their ethical skills.	10 min

The ethical scenarios presented in the workshops will have characteristics such as realism, challenge, moral significance, ambiguity, value conflicts, feedback responsiveness, flexibility, and an emphasis on active decision‐making [26]. These features are crucial in ethics education as they help students familiarize themselves with complex and common situations in the nursing profession, deepening their understanding of ethical principles. Furthermore, the presence of ethical conflicts and ambiguity in the scenarios enhances students' critical thinking and decision‐making skills and, through feedback and outcome analysis, provides an opportunity for the improvement of their ethical competencies [21, 22].

#### Postworkshop Educational Support and Follow‐Up

2.4.2

After the workshops, the materials taught to the students, including the prepared slides, ethical scenarios, and the topics discussed in the sessions, will be shared on the WhatsApp group to ensure easy access and continuous review of the content. Additionally, on the second day after the completion of the workshop, a comprehensive training booklet will be provided to the students. This booklet will include the principles and concepts of ethics, practical examples, and supplementary explanations, serving as a thorough resource for review and deeper learning. Notably, the booklet was approved by five faculty members who specialize in teaching ethics and have expertise in the field of ethics. These actions are designed to strengthen the learning process and ensure students can continue to review the educational content even after the workshops conclude.

Students will be encouraged to engage in discussions and exchange ideas about the educational content through the WhatsApp group, allowing them to raise questions, which will help sustain the learning process and deepen their ethical knowledge. The WhatsApp group will provide students with the opportunity to share their questions and opinions regarding the scenarios presented in the workshops and resolve any ambiguities. This communication platform, with its focus on ethical scenarios, will enable students to analyze and review the issues raised during the workshops and explore different solutions to the ethical challenges posed in the scenarios.

The WhatsApp discussions were moderated by the research assistant with supervision from the ethics faculty member. These discussions aimed solely to reinforce educational content and promote student reflection. No qualitative data from these interactions were analyzed, recorded, or used in the outcome assessment, to protect participant confidentiality and focus the analysis on the primary quantitative outcome.

Furthermore, discussing various experiences and perspectives related to the scenarios will help students gain a deeper understanding of ethical principles and their application in real‐world situations. This scenario‐based approach will contribute to the continuation of learning and the enhancement of their ethical decision‐making skills [27, 28].

The scenario‐based approach will be designed in such a way that in both workshops, the analysis of ethical cases will play a central role. This method is expected to strengthen students' ethical reasoning and confidence in moral action, as reflected by improvements in their professional moral courage. All the educational materials and scenarios presented during the workshops will be shared in the WhatsApp group after the sessions to facilitate further review and analysis.

The interaction among students in the WhatsApp group will continue, allowing them to share their analyses and opinions on new scenarios. Through the exchange of knowledge and experiences, students will be able to further enhance their learning.

This structure, by increasing the stages and focusing on deeper analyses, will aid in improving the students' analytical and decision‐making skills, thereby strengthening their preparation to face ethical challenges in real‐world settings [27].

After the completion of the workshops, the intervention group students will be followed up weekly for 3 months to reinforce and consolidate the training provided, with a focus on ethical scenarios. During these follow‐ups, new ethical scenarios will be sent each week for the students to analyze and evaluate. Additionally, videos and segments from educational films, designed based on similar scenarios, will be provided to strengthen students' understanding of ethical challenges and how to address them.

This scenario‐based approach will allow students to consistently encounter complex ethical situations and improve their decision‐making skills. Throughout this period, any questions and uncertainties related to the scenarios will be addressed in the WhatsApp group, where students will be encouraged to share their opinions and analyses of the scenarios and the ethical challenges presented. This emphasis on scenarios will ensure that students' active and continuous learning is maintained, enhancing their practical and applicable understanding of ethical concepts [26].

The SPIRIT 2013 template [29] describes the study schedule enrollment, interventions, and assessments (Table 2).

**Table 2 hsr271021-tbl-0002:** Schedule for enrollment, interventions, and assessments in this study.

[figure not shown]

*Note:* Background variables were collected to describe the sample characteristics and to identify potential confounders that may influence ethical reasoning and moral courage. “Overall GPA” refers to the participants' cumulative grade point average at the time of enrollment in the study.

#### Traditional Training

2.4.3

The students in the control group will not receive the scenario‐based intervention program designed for the intervention group. However, they will receive the traditional training in ethics routinely offered at the university, which consists of the “Professional Ethics and Communication Skills” course. This course is part of the standard nursing curriculum, typically delivered during the second semester, and is presented through lectures. It covers essential topics such as ethical principles (e.g., beneficence, nonmaleficence, autonomy, justice), communication strategies, and professional behavior. The content is primarily theoretical, instructor‐centered, and does not include interactive or scenario‐based activities. Meanwhile, the students in the intervention group will receive, in addition to this traditional training, a scenario‐based ethics training program. Furthermore, all educational materials related to the intervention will be provided to the control group after the study is completed and after the primary outcome variable has been measured.

### Outcome Measure

2.5

The effectiveness of the 3‐month intervention will be evaluated through the following outcome variables.

#### Primary Outcome

2.5.1

The primary outcome of this study will be:

*The professional Moral Courage of Nursing Students will be assessed by the Professional Moral Courage Questionnaire.*

The Professional Moral Courage Questionnaire [14] is used to measure moral courage in professional and workplace environments. It consists of 15 items across five dimensions: Ethical Principles, Multiple Values, Risk or Threat Tolerance, Beyond Compliance, and Ethical Goals, rated on a 7‐point Likert scale. Scores range from 15 to 105, with classifications of *Low* (< 50), *Moderate* (50–70), and *High* (> 70) Moral Courage.

The validity and reliability of the tool have been confirmed through previous studies. Construct and content validity were established by Sekerka et al. [14], and the tool demonstrated high internal consistency, with a Cronbach's *α* exceeding 0.8.

In the Iranian population, Hatami and Naderi Beni verified the validity and reported a Cronbach's *α* of 0.977 [30]. Before the study face validity of the tool will be reviewed by ten faculty members from Tehran University of Medical Sciences.

### Data Collection

2.6

In this study, data will be collected using two questionnaires: a demographic information questionnaire and the Professional Moral Courage questionnaire by Sekerka et al. [14]. The demographic information of the students will be gathered through a written questionnaire at the beginning of the study. Data on the dependent variable (Professional Moral Courage) will be collected immediately before the workshop, immediately after the workshop, 1 month later, and 3 months after the intervention. Both the intervention and control groups will be assessed for this variable, and they will complete the standardized Professional Moral Courage questionnaire by Sekerka et al. [14] in person using printed paper and pencil.

To prevent information leakage and sample contamination, the control group will complete the study first, followed by the intervention group.

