**Methods and Analysis:**

This RCT involved a 3‐month scenario‐based ethics training program delivered under faculty supervision, targeting sixth‐semester undergraduate nursing students. Participants (*n* = 48) were randomly assigned to either the intervention group or the control group. Both groups received traditional ethics education, however, the intervention group also participated in two workshops focused on core and derived ethical concepts (e.g., autonomy, confidentiality) utilizing a scenario‐based approach. This was followed by weekly online follow‐ups and discussions conducted via WhatsApp Messenger. The outcomes will be assessed using the Sekerka Professional Moral Courage Questionnaire at four time points: immediately before, immediately after, and at 1 and 3 months postintervention. The questionnaire has demonstrated acceptable validity and reliability in previous studies, with Cronbach's *α* exceeding 0.8, and a value of 0.977 reported in an Iranian validation study. In this study, face validity was confirmed by ten nursing faculty members. The data will be analyzed using *t*‐tests, *χ*
^2^ tests, and ANCOVA to evaluate changes in professional moral courage (SPSS v22, *p* < 0.05).

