### Sample Size

2.7

The sample size for this study was calculated using G*Power software (version 3.1.9.4), based on the standard formula for comparing means between two independent groups:

$$n={\left(Z(\alpha /2)\right)+Z_{\beta })}^{2}\cdot \left(\sigma_{1}^{2}+\sigma_{2}^{2}\right)/\Delta^{2}.$$

The calculation was informed by the findings of a previous study conducted by Hosseini Yazdan Abad Sofla et al. [31], which reported an effect size of 1.18. Using a significance level of 0.05 and a statistical power of 0.95, the required sample size was estimated at 40 participants. To account for an anticipated 20% attrition rate, the sample size was increased to 48 participants, ensuring adequate power to detect the expected effect even with potential dropouts.

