### Statistical Analysis

2.12

The statistical analysis plan and reporting approach in this protocol follow the Statistical Analyses and Methods in the Published Literature guidelines (SAMPL) to ensure transparency, accuracy, and consistency in the presentation of all statistical information. To describe quantitative variables, mean and standard deviation will be utilized, while frequency tables, including percentages, will be employed for qualitative variables. The Kolmogorov–Smirnov test will be used to assess the normality of the data distribution. To compare quantitative and qualitative variables between the two groups before the intervention, the independent *t*‐test and *χ*
^2^ test will be applied, respectively. Additionally, the paired *t*‐test will be used to evaluate the effectiveness of the intervention in the control and intervention groups. Analysis of covariance (ANCOVA) will be conducted to control for the effects of confounding variables. Data analysis will be performed using SPSS software version 22, and a significance level of *p* < 0.05 will be considered statistically significant for all tests.

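### The primary outcome has three post-baseline visits, no primary one and a 0.05 level for every test, and the visits are counted from conflicting starting points

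*Protocol article*

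**What the plan says.** - **Outcome (2.5.1).** The primary outcome is the Professional Moral Courage Questionnaire score, range 15 to 105. No visit is named, and the section does not say whether the final score or the change is meant. The hypothesis at the end of the Introduction names no time either.
- **Visits.** Data Collection (2.6) sets them at "immediately before the workshop, immediately after the workshop, 1 month later, and 3 months after the intervention", and Data Management (2.11) uses the same mixture of starting points. The Abstract has "immediately before, immediately after, and at 1 and 3 months postintervention".
- **What the intervention is.** Interventions (2.4) states: "The intervention consists of two workshop sessions, online education"; the same sentence also counts the follow-up contacts and gives the whole a length of 3 months. Section 2.4.2 adds that after the workshops "the intervention group students will be followed up weekly for 3 months". Section 2.5 also speaks of a 3-month intervention.
- **Sample size (2.7).** It uses the "standard formula for comparing means between two independent groups", with a standardised effect of 1.18 taken from an earlier study. The result is given as follows: "Using a significance level of 0.05 and a statistical power of 0.95, the required sample size was estimated at 40 participants". This was then raised to 48 for attrition.
- **Analysis (2.12).** Paired t-tests within each group are to judge effectiveness, and ANCOVA is to control for confounders. Neither is tied to a visit. A level of p < 0.05 "will be considered statistically significant for all tests".

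**The concern.** The trial is sized as though one comparison decides it, but the text does not say which. With three later visits and an unadjusted 0.05 level for every test, a significant result at any one of them would satisfy the hypothesis as worded. The error rate of the overall claim would then exceed 5%.

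The timing conflict makes this worse. A score taken at the end of weekly reinforcement and a score taken three months after reinforcement stops answer different questions: the effect at the end of the programme, and retention. A reader of the results could not tell which one the protocol meant. The control class has no workshop and completes the study first (2.6, 2.8), so visits placed just before and just after the workshop have no stated date in that class.

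**Working it through.** **1. Reproduce the plan's figure.** Inputs from 2.7: standardised effect 1.18, alpha 0.05 (two-sided, since the printed formula uses Z at alpha/2), power 0.95. Equal arms are assumed.

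- Normal formula: n per arm = (1.960 + 1.645)² × 2 / 1.18² = 18.7, so 19 per arm, 38 in all.
- Exact noncentral t: 19 per arm gives power 94.3% and 20 per arm gives 95.3%, so 20 per arm, **40 in all**.
- Attrition: 40 × 1.2 = 48.

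The stated 40 is reproduced. It is the size for one comparison tested once at 0.05.

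**2. Error rate if each of the three later visits is tested between groups at 0.05.**

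- Independent tests: 1 − 0.95³ = 14.3% (upper bound 3 × 0.05 = 15%).
- Three equally correlated test statistics, each significant when |z| > 1.96:

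| Correlation between test statistics (assumed) | At least one false positive |
|---|---|
| 0 | 14.3% |
| 0.5 | 12.5% |
| 0.7 | 10.9% |
| 0.8 | 9.8% |

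- Simulated baseline-adjusted ANCOVA at each visit under no effect (20,000 runs per setting; 20 and 24 per arm; equal or autoregressive correlation between scores, 0 to 0.9, assumed): about 11% to 14.5% for any false positive, and about 5.5% to 7.4% for one favouring the intervention. The single-test values are 5% and 2.5%.

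The ANCOVA figures stay fairly high because baseline adjustment removes much of what the visits share. With equal correlation ρ between scores, the correlation left after adjustment is ρ/(1 + ρ). At ρ = 0.9 this is 0.9/1.9 = 0.47.

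**3. Visit times under each wording, in months from the workshop.**

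| Visit | 2.6 and 2.11 | Abstract, taking the intervention as the 3-month programme |
|---|---|---|
| 1 month | 1 (counted from the workshop) | 3 + 1 = 4 |
| 3 months | 3 + 3 = 6 if the intervention is the programme; 3 if it means the workshop | 3 + 3 = 6 |

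Under 2.6 and 2.11 the 1-month visit falls while the weekly programme is running. Under the Abstract, read with 2.4, it falls after the programme has ended. The last visit moves by three months between readings.

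**4. What each repair costs in numbers.**

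- One primary visit at 0.05: 40 evaluable, as planned.
- Three co-equal visits with Bonferroni, 0.05/3 = 0.0167: 25 per arm (power 95.1%), 50 evaluable. That is 50 × 1.2 = 60 enrolled by the article's method, or 50/0.8 = 62.5, so 63, if 20% are lost. At 0.0167, power per visit is 88.4% with 20 per arm and 94.1% with 24.

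**The case against.** **The schedule may be clear elsewhere.** Table 2 and Figure 1 could not be seen and may give calendar times. That is a fair limit, but the prose of the Abstract, 2.6 and 2.11 would still need reconciling.

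**A coherent reading exists.** If every visit runs from the workshop, the last one coincides with the end of the weekly follow-up, and no section mentions month 6 or a retention phase. This may well be what is meant. Month 6 is only the literal result of the wording, and a reader should not infer that a six-month schedule was intended. Nor does the Abstract equate the workshop with the whole intervention; its timing phrase does not mention the workshop.

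**Multiplicity belongs in the analysis plan.** In part this stands. A multiplicity rule or a joint model could sit in a plan not shown, and its absence here is no fault. But the primary time point is part of the outcome definition, and the 0.05 rule for all tests is stated in this article.

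**Stronger readings the text does not support.** A reader might infer that the endpoint itself is undefined; the instrument and its scoring are fixed, and only the deciding visit is open. A reader might infer that a test at every visit is planned; 2.12 permits this but does not say so. Nor does 2.12 list which paired tests will be run, so no count of them can be given.

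**Conclusion.** The point holds as a gap in the primary outcome definition and a conflict in visit timing. The trial is sized for one comparison but leaves open which of three visits supplies it, under a rule that lets each be tested at 0.05. If all three are tested between groups, the overall false-positive rate is roughly 10% to 14%, or about 5.5% to 7.4% in the favourable direction against 2.5% for one test. The correlations behind these ranges are assumed, and 14.3% is the independence figure rather than the expected one. The figures also assume individually randomised students. Allocating two whole classes by a coin flip (2.8, 2.9) makes the nominal 0.05 unreliable even for a single test, so the figures only illustrate the added effect of multiple visits.

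The timing conflict depends on none of these assumptions: the last visit is at about month 3 or about month 6 depending on which sentence is followed. The point should be corrected before analysis.

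**What to change.** 1. Choose one starting day for all visits, for example the second workshop day with a matched date in the control class. Restate every visit from it in the Abstract, 2.6 and 2.11.
2. In 2.5.1, name one primary visit. Whether it is the end of the programme or later retention is the sponsor's choice, since the two answer different questions.
3. In 2.12, make the baseline-adjusted between-group comparison at that visit, using the ANCOVA already planned, the single test at 0.05.
4. Report the other visits and the within-group paired t-tests as secondary, without confirmatory claims. A repeated-measures model is optional.

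The cost is wording: no extra data, and the 40 evaluable students stand. The downside is that the other visits can no longer carry the claim. If the sponsor wants all three to do so, a multiplicity rule is needed, and under Bonferroni that means 50 evaluable students for the same power. None of this addresses the one-class-per-arm design, which needs separate treatment.
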